### Sample Size Estimation

The sample size was powered based on the mean reduction in body weight (kg) to provide greater statistical sensitivity than binary outcomes. Drawing from meta-analyses of digital interventions for SMI [8] and the recent CoachToFit trial [32], a Cohen *d* of 0.40 was identified as a clinically realistic target effect size. Using PASS 2021 (stepped-wedge cluster-randomized design module) with 6 clusters and monthly repeated measurements, a total sample of 204 participants (34 per unit) provides 82% power (α=.05, 2-tailed) assuming a conservative intracluster correlation coefficient (ICC) of 0.10. This value is consistent with empirical benchmarks for metabolic outcomes in psychiatric institutional settings [43-45]. Furthermore, this sample size is sufficiently robust to detect the primary categorical outcome of ≥5% weight loss, assuming a 20% success rate in the control phase and a 40% success rate in the intervention phase (odds ratio≈2.6). Accounting for a 20% attrition rate (aligned with recent SMI trial observations), the final evaluable sample (n=163) maintains ≥75% power even under varying cluster performance, ensuring robust detection of the treatment effect under pragmatic constraints.

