### Primary Objective

The primary objective is to evaluate the effectiveness of the digital intervention on body weight reduction. The primary outcome is the proportion of participants achieving ≥5% weight loss at the end of the intervention phase compared to the control phase. This threshold, along with the ≥7% threshold, is selected based on established evidence linking these levels of weight loss to significant cardiovascular and metabolic health benefits in the SMI population [28-31]. Based on recent trials of tailored digital interventions in similar populations, which reported ≥5% success rates ranging from 15% to 36.6% [32], we anticipate that the intervention will achieve a success rate of at least 40%, significantly higher than the expected 20% success rate in the control phase.

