#### Clinical Effectiveness Analysis

To account for the nested cluster structure and secular time trends inherent in the stepped-wedge design, we use 2 complementary modeling approaches. For the primary binary outcome (≥5% weight loss), a generalized estimating equations model with a logit link function will be used to compare proportions across study phases. For continuous secondary outcomes (eg, mean percentage weight change and BMI reduction), we will use a Linear Mixed-Effects Model. The model is specified as follows:

Yijk=β0+β1⋅Interventionjk+Σγk⋅Timek+Σδm⋅Covariatesijk+αj+ζij+ϵijk

Where:

Yijk represents the continuous outcome for individual i in cluster j at time k.β1estimates the treatment effect (Intervention vs Control); γk represents categorical secular time trends to isolate the intervention’s impact from time-related fluctuations; and δm denotes fixed-effect adjustments for the prespecified covariates. αj is the random intercept for the cluster (clinical unit) to account for ICC; ζij is the random intercept for the individual to account for repeated measurements over time; and ϵijk represents the residual error.

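### One sample size is supported by two effect sizes that disagree: d=0.40 for mean weight, but 20% versus 40% (d about 0.54 to 0.59) for the binary primary outcome

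*Protocol article*

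**What the plan says.** Sample Size Estimation opens with "The sample size was powered based on the mean reduction in body weight (kg) to provide greater statistical sensitivity than binary outcomes". A Cohen's d "of 0.40 was identified as a clinically realistic target effect size". The calculation is attributed to a stepped-wedge module "with 6 clusters and monthly repeated measurements" and an ICC of 0.10, and the result is that "a total sample of 204 participants (34 per unit) provides 82% power (α=.05, 2-tailed").

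The section then turns to the primary outcome and says that "this sample size is sufficiently robust to detect the primary categorical outcome of ≥5% weight loss, assuming a 20% success rate in the control phase"; the matching intervention rate is 40%, with a printed odds ratio of about 2.6. It gives no power figure for that comparison and does not relate the two rates to d=0.40. The closing sentence gives at least 75% power at n=163 after 20% attrition, without naming the outcome or the effect.

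The Primary Objective uses the same rates: "we anticipate that the intervention will achieve a success rate of at least 40%, significantly higher than the expected 20% success rate" under control conditions. The trials it cites reported success rates of 15% to 36.6%. Under Clinical Effectiveness Analysis, the primary outcome is analysed as a binary variable: "For the primary binary outcome (≥5% weight loss), a generalized estimating equations model with a logit link function will be used".

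**The concern.** The trial is sized on a secondary outcome, and its adequacy for the primary outcome is then asserted under a different and larger effect. Both assumptions concern what the same intervention does to body weight, so they should be compatible, and the protocol does not show that they are.

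The section's own reasoning points to the problem. It chooses the continuous outcome because binary outcomes are less sensitive, yet under its stated inputs the binary outcome comes out with more power than the continuous one (see the working). For a dichotomised version of the same variable with equal spread, that reversal can come only from a larger assumed effect.

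The interpretation of the primary result is at stake. Someone who carries the printed power over to the primary outcome will read a null result as stronger evidence against a d=0.40 effect than the design can supply.

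**Working it through.** **Inputs.** From Sample Size Estimation: d=0.40, N=204, two-sided α=0.05, 82% power, 20% versus 40%, n=163 after attrition. Assumptions not in the documents: weight change is normal or logistic, with equal SD in both conditions.

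**1. The printed 82%.** A two-group z formula with 102 per group and no clustering gives Φ(0.40·√51 − 1.96) = 81.5%. This matches 82%, but it ignores the ICC of 0.10. Stepped-wedge (Hussey-Hughes) variants with ICC 0.10 do not settle on 82%:
- 29-35% if the 34 per unit are split over periods
- 71-95% if 34 are measured in every cluster-period
- 94% or more for a closed cohort with individual autocorrelation of at least 0.5

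The article does not give the layout that was entered, so the 82% is taken at face value below.

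**2. What 20% versus 40% implies on the d scale.**
- Normal: Φ⁻¹(0.40) − Φ⁻¹(0.20) = −0.253 + 0.842 = 0.588.
- Logistic: odds ratio (0.40/0.60)/(0.20/0.80) = 2.67; d = ln(2.67)·√3/π = 0.541.

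These exceed 0.40 by 35% (0.541/0.40) to 47% (0.588/0.40).

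**3. What d=0.40 implies for responders from a 20% control rate.**
- Normal: Φ(−0.842 + 0.40) = 32.9%, odds ratio 1.96.
- Logistic: odds ratio exp(0.40·π/√3) = 2.07, rate 34.1%.

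**4. Standardised binary effect**, (p₂ − 0.20)/√{[0.16 + p₂(1−p₂)]/2}:

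| p₂ | Standardised effect | Ratio to 0.40 |
|---|---|---|
| 32.9% | 0.296 | 0.74 |
| 34.1% | 0.321 | 0.80 |
| 40% | 0.447 | 1.12 |

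**5. Scaling the printed 82%.** The noncentrality behind 82% is 1.960 + 0.915 = 2.875.
- Normal: 2.875 × 0.296/0.40 = 2.13; Φ(2.13 − 1.96) = 57%.
- Logistic: 2.875 × 0.321/0.40 = 2.30; Φ(2.30 − 1.96) = 63%.

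This step also assumes similar within-unit correlation on the two scales.

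**6. Unclustered cross-check** (two-proportion formula; comparison only, not the trial's power):

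| Comparison | N=204 | n=163 |
|---|---|---|
| Mean weight, d=0.40 | 81.5% | 72.4% |
| 20% vs 32.9% | 55.4% | 46.5% |
| 20% vs 34.1% | 62.0% | 52.4% |
| 20% vs 40% | 88.2% | 80.1% |

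The binary outcome beats mean weight only in the last row, where the effect is larger. In the stepped-wedge variants of step 1, the binary outcome at d=0.40 was below the continuous one wherever power was not already near 100%.

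**The case against.** The protocol attaches 82% to mean weight only. A reader might infer that it claims 82% for the primary outcome, or that the binary sentence contains an arithmetic error. The text supports neither. The sentence states its 20% and 40% assumption openly, and at those rates the unclustered formula gives 88%. What stands against the protocol is that two disclosed assumptions are not reconciled.

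The conversion is not forced either. The sizing outcome is kilograms with repeated measurements, whereas the primary outcome is percentage loss at month 6. Equal spread is an assumption. Under a normal model with d on the pooled SD, an intervention SD about 1.4 times the control SD would make d=0.40 and 20% versus 40% agree exactly. The protocol states no such difference in spread, but the objection stands as a limit on the point, and the disagreement must be described as conditional on a common SD.

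A reader might also take 57-63%, or the unclustered 55-63%, as the power of this trial. Neither is. The first inherits whatever produced the printed 82%, and the second ignores clustering, periods and repeated measures. The direction is better supported than the size.

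It is also tempting to say that the figure of at least 75% at n=163 belongs to mean weight. The text does not say so: it follows the binary claim directly, and the unclustered check gives 72.4% for mean weight and 80.1% for 20% versus 40%. The attribution is open.

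Finally, the Statistical Plans put estimation ahead of testing and use 80% CIs for clinical effects. That softens the consequence, but an explicit adequacy claim for the primary outcome remains in the text.

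**Conclusion.** The point holds as an unreconciled pair of effect sizes. Under a common-SD normal or logistic model, the adequacy claim for the primary outcome needs an effect 35-47% larger than the d=0.40 that the protocol calls realistic, and a response rate above the top of its cited range (36.6%). At d=0.40 with a 20% control rate, about 33-34% would reach 5% loss, and power for the primary outcome is clearly lower than for mean weight. If the printed 82% is accepted, the corresponding figure is roughly 57-63%, given equal spread and similar within-unit correlation. The documents do not allow a firm absolute power for the primary outcome, and none is asserted here.

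**What to change.** In Sample Size Estimation, replace the adequacy sentence with power for the binary primary outcome from the same stepped-wedge calculation (6 clusters, ICC 0.10, month-6 outcome). Give it twice: at the rate implied by d=0.40 from a 20% control rate (about 33-34%), and at 20% versus 40% labelled as an optimistic scenario. State that 82% refers to mean weight reduction, and state which outcome and effect the figure of at least 75% at n=163 refers to. Align the expectation of at least 40% in the Primary Objective with this. Do not print unclustered figures as the trial's power.

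The cost is one rerun of an existing calculation and a few sentences. Recruitment of 204 is complete, and no patients or data are added. The stated power for the primary outcome at d=0.40 will probably look less favourable.

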### Statistical Plans

#### Overview

All analyses will follow the intention-to-treat principle. We prioritize effect size estimation over formal hypothesis testing. Implementation outcomes, including recruitment, retention, and adherence rates, will be reported with 95% CIs. For clinical intervention effects, we will report point estimates with 80% CIs to balance precision with exploratory use, as wider intervals better reflect the preliminary nature of these estimates and minimize the risk of overinterpreting early trends. To account for the different intervention durations between waves, intervention exposure duration (time since crossover) will be included as a time-varying covariate in the mixed-effects models. This approach allows for the estimation of the intervention effect while adjusting for the varying lengths of exposure across clusters.

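### Clinical effects are to be reported with 80% confidence intervals because these are said to be wider, but they are 35% narrower than 95% intervals and miss a true null 20% of the time

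*Protocol article*

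**What the plan says.** The overview of the statistical plans sets two interval levels. For process measures: "Implementation outcomes, including recruitment, retention, and adherence rates, will be reported with 95% CIs". For clinical effects, in the next sentence: "we will report point estimates with 80% CIs to balance precision with exploratory use, as wider intervals better reflect the preliminary nature". That sentence goes on to say that the wider intervals will "minimize the risk of overinterpreting early trends".

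The same section states: "We prioritize effect size estimation over formal hypothesis testing". Sample Size Estimation is framed at the conventional level: 204 participants "provides 82% power (α=.05, 2-tailed) assuming a conservative intracluster correlation coefficient (ICC) of 0.10".

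No part of the article gives another sense in which an 80% interval would be the wider one. The only comparator nearby is the 95% level in the preceding sentence.

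**The concern.** Lowering the confidence level shortens an interval. The plan chooses the lower level and justifies it with a property that only a higher level has. A reader who trusts the stated reason will take these intervals to be more cautious than usual, when they are less so.

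This matters because formal testing is played down, so the interval carries the inference. Readers will take an interval that excludes no effect as evidence of benefit or harm. That applies to the primary outcome (at least 5% weight loss at month 6) and to a long list of clinical and psychosocial secondary outcomes.

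The level is also out of step with the trial's size. An 80% interval corresponds to a two-sided error of .20, whereas the sample size was justified at .05.

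**Working it through.** The article gives no figure for interval width, so there is none to reproduce. The check needs only the two confidence levels.

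**Inputs**
- Level for clinical effects: 80%, two-sided error 0.20 (Statistical Plans, Overview).
- Comparison level: 95%, two-sided error 0.05 (implementation outcomes in the same paragraph; alpha in Sample Size Estimation).
- Clusters: 6 (Sample Size Estimation). This matters only if t critical values are used. The article gives no degrees of freedom, so those below are assumptions.

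**Width.** An interval is the estimate ± critical value × SE. With the same SE, the width ratio is the ratio of critical values:
- z(0.90) / z(0.975) = 1.2816 / 1.9600 = 0.654, so the 80% interval is 34.6% narrower.
- In the other direction, 1.9600 / 1.2816 = 1.53, so a 95% interval would be 53% wider.

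For the primary outcome, modelled with a logit link, these ratios apply on the log-odds scale.

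| Critical values | 80% | 95% | Ratio | Narrower by |
|---|---|---|---|---|
| Normal | 1.282 | 1.960 | 0.654 | 34.6% |
| t, 202 df | 1.286 | 1.972 | 0.652 | 34.8% |
| t, 161 df | 1.287 | 1.975 | 0.652 | 34.8% |
| t, 5 df | 1.476 | 2.571 | 0.574 | 42.6% |
| t, 4 df | 1.533 | 2.776 | 0.552 | 44.8% |

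The 35% figure is therefore the low end.

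**Exclusion of a true null.** The probability is 2 × (1 − Φ(z)):
- 80%: 2 × (1 − Φ(1.2816)) = 0.200. One million simulated null draws gave 0.199.
- 95%: 2 × (1 − Φ(1.9600)) = 0.050. The same draws gave 0.050.

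The difference, 0.20 − 0.05 = 0.15, is the share of null results whose 80% interval excludes no effect while the 95% interval does not.

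**Across outcomes.** Secondary Outcomes names body weight, BMI, body fat, fasting glucose, lipids (counted here as one), ten psychometric scales and a motivation scale. That is 5 + 10 + 1 = 16, or 17 with the primary outcome. If all were truly null, the expected number of intervals excluding no effect would be 17 × 0.20 = 3.4 at the 80% level and 17 × 0.05 = 0.85 at the 95% level. These expectations do not require the outcomes to be independent.

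**The case against.** The strongest defence is that an 80% level is a legitimate choice for preliminary estimation. The article calls the effectiveness evidence preliminary, describes the trial as a proof of concept, and ranks clinical implications above nominal significance. Sizing a trial at alpha .05 does not by itself dictate the reporting level. It follows that 80% is not wrong in the abstract. This does not rescue the text, because the plan gives its own reason for the choice (wider, more cautious intervals), and 95% meets that reason while 80% does not.

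Four narrower points stand in part:
- The 95% intervals elsewhere in the paragraph are for descriptive rates, not treatment effects. Different levels for different quantities are an inconsistency of standard, not a contradiction.
- The 20% is two-sided: a null effect appears as a benefit about 10% of the time and as a harm about 10%.
- A false discovery rate correction is planned for secondary and subgroup analyses. That tempers the multiplicity argument, but the correction does not widen the reported intervals.
- With normal-based intervals a reader can multiply the half-width by 1.53 to recover the 95% interval. That helps only a reader who knows the stated rationale is wrong.

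A caution runs the other way: moving to 95% does not guarantee 95% coverage with 6 clusters. The article names a GEE for the primary outcome without saying which variance estimator is used, and a fuller plan may settle this. As a rough analogue, take a 3-versus-3 cluster contrast with an uncorrected sandwich variance (factor 2/3, 4 df; all assumed). The false exclusion rate is then P(|t₄| > 1.2816 × √(2/3)) = P(|t₄| > 1.046) ≈ 35% at nominal 80%, and P(|t₄| > 1.600) ≈ 18% at nominal 95%. That is a separate issue from the interval level, and the conclusion here does not rest on it.

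**Conclusion.** The concern holds. The stated rationale is the opposite of what the chosen level does: the planned intervals are 35% narrower than 95% intervals (43 to 45% narrower if t critical values on 5 or 4 df are used) and nominally exclude a true null 20% rather than 5% of the time. The width figure assumes only that both intervals use the same standard error. The 20% and 5% figures also assume that the standard error is correctly estimated, and they apply per estimate.

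Because the level governs every clinical interval, including that of the primary outcome, and the plan relies on intervals rather than tests, this must be corrected before results are reported.

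**What to change.** Report 95% confidence intervals for all clinical intervention effects, in line with the two-tailed alpha of .05 in Sample Size Estimation and the level already set for implementation outcomes. Delete the statement that 80% intervals are wider and limit overinterpretation. If 80% intervals are still wanted, give them as a labelled supplement and state that they are narrower and have 20% nominal non-coverage.

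The Results section says that initial analysis is in progress. The change should therefore be dated, with a note of whether any effect estimates had been seen.

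The cost is one sentence and wider reported intervals (1.53 times the width under normal critical values). No new data are needed, and the models and point estimates stay the same.

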#### Covariate Adjustment and Confounder Control

Following the framework established by Chinman [32], the models will control for critical pharmacological and clinical confounders. To account for the different intervention durations between waves, intervention exposure duration will be included as a time-varying covariate. Antipsychotic treatments will be categorized into high-risk (eg, clozapine and olanzapine) and low-to-moderate risk groups, also incorporated as time-varying covariates to account for any regimen changes during the 6-month period. To isolate the intervention’s effect from “pseudo-weight loss” caused by medication nonadherence, medication possession ratios will be calculated; participants with a medication possession ratio <80% will be analyzed as a separate subgroup in sensitivity analyses. Additionally, stratified analyses based on baseline weight status (overweight vs obese) will be conducted to explore potential moderating effects.

Missing data will be addressed via multiple imputation under missing at random assumptions. Further sensitivity analyses, including pattern mixture models and tipping point analysis, will be performed to evaluate the impact of potential missing not at random mechanisms. To mitigate the risk of type I error inflation across multiple secondary and subgroup analyses, the false discovery rate correction will be applied. All analyses will be conducted using SAS 9.4, with clinical and feasibility implications prioritized over nominal statistical significance.

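### With time since crossover in the mixed models, β1 is the effect at zero exposure, but the plan reads it as the treatment effect

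*Protocol article*

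**What the plan says.** The Statistical Plans overview states that "intervention exposure duration (time since crossover) will be included as a" time-varying covariate in the mixed-effects models. It gives the reason: "This approach allows for the estimation of the intervention effect while adjusting for the varying lengths of exposure across clusters".

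Clinical Effectiveness Analysis displays the linear mixed model for continuous outcomes. It has an intervention indicator with coefficient β1, categorical time, a sum of covariate terms, and random intercepts for unit and individual. β1 is described as the effect of intervention against control. The time term "represents categorical secular time trends to isolate the intervention’s impact from time-related fluctuations", and the δ coefficient "denotes fixed-effect adjustments for the prespecified covariates". The primary binary outcome has its own GEE model with a logit link.

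Covariate Adjustment and Confounder Control repeats, for the models in general, that "intervention exposure duration will be included as a time-varying covariate". It also says that antipsychotic risk groups are "also incorporated as time-varying covariates to account for any regimen changes during the 6-month period".

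The article states no centring of exposure, no combination of β1 with the exposure slope, and no exposure at which the effect is to be read.

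**The concern.** Time since crossover is 0 in every control period and counts up only after the unit has crossed over. It therefore measures how much treatment has been received and is not a confounder of treatment. When it stands beside the indicator, the benefit that accumulates goes into the exposure slope θ, and β1 keeps only the fitted jump at the moment of crossover. The overview presents the adjustment as a way to obtain the intervention effect, but β1 alone is then not that effect.

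The plan puts effect estimation ahead of testing, so the meaning of the reported coefficient matters. An intervention that works through gradual behaviour change could be reported with an estimate of zero, or with the wrong sign.

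Drug class raises a separate question. It is updated after crossover, so it is a post-randomisation variable. Adjusting for it removes any part of the effect that runs through regimen changes, which fits poorly with the intention-to-treat principle stated in the overview.

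**Working it through.** **Inputs from the article.** Three units per wave; intervention for 5 months in wave 1 and 3 months in wave 2 (Study Design); visits at months 0, 1, 2, 3 and 6 (Outcomes and Measures, Overview); 34 participants per unit and ICC 0.10 (Sample Size Estimation); categorical time (Clinical Effectiveness Analysis).

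**Assumptions.** Exposure is counted from month 1 (wave 1) or month 3 (wave 2), so that it is 5 and 3 at month 6. The effect shapes, the 4 kg size, unit autocorrelation 0.8 to 1.0 and individual autocorrelation 0.5 to 0.9 are mine. The same 34 per unit are taken as measured at each visit.

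The article gives no figure for this point. Its 82% power is not used here.

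**Step 1: what β1 means.** Let X be the indicator and E the exposure, with E = 0 whenever X = 0. The treatment part of the model is β1·X + θ·E, so the effect after e months is β1 + θ·e. At e = 0 this is β1.

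- True effect s·e: β1 = 0 and θ = s fit exactly.
- True effect s·(e − d), with all observed exposures at or beyond d: β1 = −s·d and θ = s fit exactly. The sign of β1 is then opposite to that of the effect.

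**Step 2: expected β1 on the visit schedule.** The exposed visits have e = 1, 2, 5 (wave 1) and 3 (wave 2). The true effect is scaled to −4 kg at 5 months. For linear growth, for example, the average true effect is −0.8 × (1 + 2 + 5 + 3)/4 = −2.20. Generalised least squares gives:

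| True shape | Average true effect (kg) | β1 (kg) | θ (kg/month) |
|---|---|---|---|
| Immediate | −4.00 | −4.00 | 0 |
| Plateauing, proportional to 1 − exp(−e/2) | −2.96 | −1.68 | −0.42 |
| Square root of e | −2.85 | −1.44 | −0.50 |
| Linear | −2.20 | 0.00 | −0.80 |
| None for 1 month, then linear | −1.75 | +1.00 | −1.00 |

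For the two curved shapes β1 is 1.68/2.96 = 57% and 1.44/2.85 = 51% of the average. The immediate, linear and delayed rows are exact for any correlation. The curved rows move by at most 0.01 over the range tried.

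**Step 3: leaving the exposure term out.** With a true effect of 1 unit per month, the month-6 effects are 5 and 3. The expected β1 of a constant-effect model is:

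- visits 0, 1, 2, 3, 6: 0.84 to 0.90, which is 17 to 18% of 5 and 28 to 30% of 3;
- monthly data, months 0 to 6: 0.31 to 0.38;
- monthly data, months 1 to 6: 0.01 to 0.12.

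The reason is that wave 1, already treated and still improving, serves as comparator when wave 2 crosses over.

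**Step 4: cost of the right contrast.** On the visit schedule, the SE of β1 + θ·e relative to the constant-effect SE is about 1.2 at e = 2, 1.65 at e = 3 and 2.7 at e = 5. These ratios barely change with the correlations.

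**Step 5: drug class.** Assume a 2 kg difference between risk classes. If crossover lowers high-risk use by 10 or 20 percentage points, the part removed by adjustment is 2 × 0.10 = 0.2 kg or 2 × 0.20 = 0.4 kg. A small simulation agreed. With no shift in prescribing, nothing is removed.

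**The case against.** The best defence is that the article does not give the effect's shape, and that centring and contrast statements are often left to an analysis plan, which is not shown here. It is true that β1 is unbiased if the effect is immediate. But the article does more than leave a detail open: it says what β1 estimates, and with the stated covariate that is wrong unless the effect is constant over exposure.

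Several stronger readings are tempting and are not supported.

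- A reader might infer that the displayed equation and the text describe two different models, because no exposure term is written out. The generic covariate sum can hold it.
- A reader might infer that any gradual effect would be reported as about zero. That needs roughly linear growth from crossover. A plateauing effect leaves β1 at about half the average.
- A reader might infer that the primary analysis is compromised. The overview ties the term to the mixed-effects models, which serve the continuous outcomes, and the later section speaks only of the models. Use in the primary GEE is unclear, not established.
- A reader might turn the SE ratios into a loss of power by applying d = 0.40 at both 3 and 5 months. That contradicts a growing effect, and it also needs autocorrelations that the article does not give.
- A reader might infer that drug class adds to the zero-exposure problem, or that dashboards change prescribing. The first is a separate matter and the article does not state the second. Entry also requires 4 weeks on a stable regimen. The size of this part is unknown and may be nil.

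**Conclusion.** The point holds for the mixed models of the continuous weight outcomes. These matter because the sample size is based on mean weight reduction. As written, β1 is the effect at zero exposure: correct for an immediate effect, roughly half the average for a plateauing one, zero for linear growth and wrong in sign after a delay. The kg figures rest on the assumed shapes and the 4 kg scale. The algebra behind the zero and the sign reversal does not, and the correlations make no material difference. A constant-effect model is no safe alternative when the effect grows.

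Whether the primary GEE is affected cannot be settled from the text. Drug class is a separate and smaller matter, with no effect on the estimate if prescribing does not shift.

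**What to change.** 1. Write the exposure term θ·E into the displayed model and state when its clock starts relative to the 2-week transition.
2. Do not report β1 alone. Report β1 + θ·e with its SE and CI at stated exposures, for example 2 months and 3 months. At the month-3 visit wave 1 has had 2 months and wave 2 is still in control. Three months is the longest exposure that both waves receive, but both are treated at month 6, so that result relies on the linear form and should say so. The month-6 primary endpoint need not move.
3. State whether the GEE uses the same term and contrast.
4. Use baseline antipsychotic risk class in the main model and keep time-varying class as a sensitivity analysis.

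This needs no new data: it is model wording and one contrast statement per exposure. The Results section says that analysis is in progress, so the change should be dated and documented. The price is precision: the SE is about 1.65 times the constant-effect SE at 3 months and 2.7 times at 5 months on the visit schedule.
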